#### Statistical methods for efficacy and secondary outcome analyses

2.10.5

First, the randomness of the samples will be verified to ensure that the baseline characteristics of the two groups do not show statistically significant differences. Univariate analysis will be conducted to identify sociodemographic and diagnostic variables that could differ between the two groups selected randomly before the study.

Continuous variables will be analyzed using Student’s t-test or the nonparametric Mann–Whitney test to compare medians when they do not follow a normal distribution. Categorical variables will be analyzed using the Chi-square or Fisher’s exact test for contrast in each case. Confounding variables will be included in the adjustment for all subsequent analyses. Logistic regression analysis will be performed to the control group and the MD-Int group. Composite scores will be calculated as *Z*-scores standardized to the Baseline mean and standard deviation (SD), with higher scores indicating better performance. The decline will be defined as a decrease in z-scores between Baseline and 24-month visit assessments (Z24month - Zbaseline < 0). Those covariables considered to influence changes in cognition will be introduced as model variables.

Third, mixed models will be used to study the trajectories of the different scores (NTBm) in the control and intervention groups. Mixed models explicitly account for the correlations between repeated measurements within each patient. The factors assumed to have the same effect across many patients are called fixed effects, and those likely to vary substantially from patient to patient are called random effects. In these mixed models, the interaction between the group variable (control vs. intervention) and the time will be included in all final analyses because the study’s final objective is to determine the effect of the intervention on effectiveness along time, adjusted for other variables that could influence them. For statistical analysis, the programs SPSS® (version 23) and R (version 4.2.3 or superior) will be used with a significance level of 95%.

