**Methods:**

It is a two-year, population-based, randomized controlled trial to prevent cognitive decline in adults aged 60–85 years with Cardiovascular Risk Factors, Aging and Dementia (CAIDE) risk score ≥6, no dementia, and below-than-expected performance on at least one of three cognitive screening tests. Participants are randomized (1:1) to receive either Regular Health Advice (RHA) or a Multidomain Intervention (MD-Int) that encompasses cognitive training, socio-emotional skills, multicomponent physical exercise, nutritional and culinary intervention, and monitoring for cardiovascular risks, pharmacological drug mismanagement, and comorbidities. The primary outcome is the efficacy of the intervention to reduce the risk of cognitive decline measured by the global composite *z*-score of the modified Neuropsychological Test Battery over two years. The secondary outcomes measure cost-effectiveness, quality of life, and functional abilities. Blood samples and brain imaging will also be collected to evaluate the effects of the intervention on brain structure and plasma biomarkers.

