### Study objectives

2.2

The primary objective is to ascertain the efficacy of the intervention to attain a 20% reduction in the proportion of subjects exhibiting a decline in cognitive performance, as measured by the change in the global cognition z-score on the modified Neuropsychological Test Battery (mNTB) (Harrison et al., 2007; Kivipelto et al., 2013), between baseline and 24 month visits in the multidomain intervention group (MD-Int) relative to the regular health advice (RHA) group. Secondary objectives include: (1) analyzing the cost-effectiveness of the intervention; (2) determining the beneficial effects of the intervention on functional abilities, quality of life, and symptoms of depression and anxiety; and (3) investigating the impact of lifestyle interventions on: neuroimaging parameters of brain volumetry, white matter integrity and vascular burden; plasma biomarkers of Alzheimer’s pathology, neurodegeneration, and neuroinflammation; epigenetic marks; lipid dysregulation; and cognitive and brain reserve capacity.

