#### Primary outcome: cognitive performance I

2.6.1

In accordance with the WWFINGERS network data harmonization recommendations, cognitive performance change is the primary outcome. It is assessed using the modified Neuropsychological Test Battery (mNTB) (Harrison et al., 2007), previously described for in our pilot study (Tainta et al., 2024a) and in Supplementary Table S3. It is recorded by trained neuropsychologists who are blinded to the group assignment at baseline evaluation and at the 12-month and 24-month visits. The mNTB Cognitive Global score is obtained. Composite cognitive z-scores are calculated based on the results of all single tests. The higher the score, the better the performance. Changes in global cognition are assessed by differences between Global Cognitive composite z-scores at baseline and 24-month visits.

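### Two primary quantities (the proportion with any z-score drop, and the mean z-score change) are stated without saying which is confirmatory, and the zero cut makes the binary one inefficient

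*Protocol article*

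**What the plan says.** Two readings of the primary outcome run through the protocol article.

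**Proportion who decline.** The abstract states: "The primary outcome is the efficacy of the intervention to reduce the risk of cognitive decline measured by the global composite" z-score of the battery. Section 2.2 makes it the primary objective to "attain a 20% reduction in the proportion of subjects exhibiting a decline in cognitive performance". The first calculation in Section 2.10.1 compares two proportions of decliners, 49% and 32%, with a one-sided test at 5%. In Section 2.10.5, "Logistic regression analysis will be performed to the control group and the MD-Int group", and the definition of decline follows: "The decline will be defined as a decrease in z-scores between Baseline and 24-month visit assessments", written as a 24-month minus baseline difference below zero.

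**Change in score.** Section 2.6.1 says "cognitive performance change is the primary outcome", and then "Changes in global cognition are assessed by differences between Global Cognitive composite z-scores at baseline and 24-month visits". Table 2 lists the global composite z-score as the primary outcome. The second calculation in Section 2.10.1 uses a two-tailed t test for a difference of 0.10 in change with SD 0.33. Section 2.10.5 adds that "mixed models will be used to study the trajectories of the different scores (NTBm) in the control and intervention groups", with a group-by-time interaction that it ties to the study's final objective.

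No section ranks the logistic regression against the mixed model, or says which of the two sidedness rules governs the conclusion.

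**The concern.** Some details can be left to a statistical analysis plan. This is different: the article itself gives two primary quantities, two tests, two sidedness rules and two sample sizes. If the choice is still open when the data are unblinded, it can no longer be shown to be independent of the results, and benefit could be claimed on whichever version succeeds.

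The binary version also has a weakness of its own. A cut at zero treats a change of -0.001 as decline and +0.001 as none. If changes are symmetric around zero, half of the participants are decliners by definition, and the planned control rate is 49%. A headline of reduced risk of decline would then rest largely on the sign of small changes, and would need more participants than the mean change does to show the same effect.

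**Working it through.** **Inputs.** 49% control decline rate, SD 0.33, difference 0.10, 20% dropout, 90% power (Section 2.10.1); 20% reduction (Section 2.2), so 0.49 × 0.80 = 0.392; 465 and 455 allocated so far (Results). Evaluable: 465 × 0.8 = 372 and 455 × 0.8 = 364. Normally distributed change scores with equal SD are my assumption.

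**1. The plan's own figures.** Two proportions, pooled variance, one-sided 5%, 90% power:
- 49% v 39.2%: 438 per arm; 438/0.8 = 548 after rounding up; total 1,096, as printed.
- 49% v 32%, as printed: 141 per arm, 177 after dropout, 354 in total.

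The printed total therefore matches the 20% reduction, and I use 39.2% below. For the continuous version (0.10, SD 0.33, two-sided 5%, 90% power) I get 229 per arm, 287 after dropout and 574 in total, not 802. These mismatches are separate matters and do not affect this point.

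**2. What a 49% decline rate means.** Mean control change = -SD × Φ⁻¹(0.49) = -0.33 × (-0.0251) = +0.008, essentially zero. Moving from 49% to 39.2% is a shift of 0.33 × (0.2741 - 0.0251) = 0.082.

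**3. Information kept by the cut.** The efficiency of a proportion p against the mean of a normal variable is φ(c)²/[p(1 - p)], with c = Φ⁻¹(p).
- p = 0.50: 2/π = 0.637, a loss of 36.3%.
- p = 0.49: 0.636, a loss of 36.4%.
- p = 0.405 (midway between 49% and 32%): 0.623, a loss of 37.7%.

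Finite-sample check: the plan's 0.10 shift, cut at zero, is 49% v 37.1%. It needs 365 per arm as proportions and 229 as means (two-sided, 90% power), and 229/365 = 0.63.

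**4. Power for the same effect, 372 and 364 evaluable.**

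| Test level | 49% v 39.2% as proportions | Shift 0.082, SD 0.33, as means |
|---|---|---|
| One-sided 5% | 85% | 96% |
| Two-sided 5% | 76% | 92% |

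**5. False claims of benefit if either analysis suffices.** With no effect, the two test statistics are correlated at about √(2/π) = 0.80.
- Both tests two-sided at 5%, benefit direction only: simulation gives about 3.8% against a nominal 2.5%. The bivariate normal calculation with that correlation gives 3.9%.
- Proportions one-sided at 5% and t test two-sided at 5%, as in Section 2.10.1: simulation gives about 5.7% (bivariate normal 5.9%). This compares with 2.5% for the t test alone and 5% for the one-sided test alone.

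**The case against.** The text leans towards the binary reading. The abstract, the central hypothesis in the Background, the primary objective and the first sample size all speak of decline, and Section 2.2 says that decline is measured by the change in z-score. On that view Section 2.6.1 and Table 2 only name the instrument and its scoring. That is a fair account of those two places. It does not explain the second sample size with its different sidedness, or the unranked mixed models.

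A reader might infer more than the article supports:

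- **That the binary analysis is invalid or underpowered.** It is neither. Raters are blinded and the same cut applies to both arms, so noise mainly dilutes the contrast. At 372 and 364 evaluable, the plan's own 0.10 shift (49% v 37.1%) has about 90% power two-sided as proportions, and the printed 49% v 32% has more than 99%. If all 1,051 selected were randomised (about 420 per arm after dropout), 49% v 39.2% would have 89% power one-sided.
- **That the false-positive rate is 7.6%.** That figure counts significant results in either direction, including harm. Nor does the article say that either analysis alone would suffice, so the rates in the working are conditional on that.
- **That a known share of participants, such as a quarter, is misclassified.** That needs the reliability of the change score, which the article does not give. An assumed reliability of 0.3 gives 32% and 0.9 gives 10%.
- **That participants without a 24-month score are dropped, or that an odds ratio will be presented as the 20% reduction.** The article states no missing-data rule and no effect measure for the logistic model. Both may be settled in the unseen analysis plan.
- **That nobody in the control arm declines.** A mean change near zero can hide individual decline, for example behind practice effects.

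**Conclusion.** The point holds in limited form and should be fixed. The article states two primary quantities with different tests and sidedness and does not say which is confirmatory. If benefit could be claimed on either, the inflation is real but modest: about 3.8% against 2.5%, or about 5.7% with the stated sidedness.

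The zero cut is a valid but inefficient way to use the score. It costs 36 to 38% of the information, or 11 percentage points of power one-sided (85% v 96%) and 16 two-sided (76% v 92%) for the 20% reduction at the numbers allocated so far. This rests on roughly normal change scores, an SD of 0.33 in both arms, 20% dropout, and 920 randomised, which may not be the final number. The comparison is with a two-visit change score. It takes no credit for the 12-month visit that the mixed model would also use.

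**What to change.** Before unblinding (the last visit is expected in autumn 2026), name one confirmatory analysis with one sidedness in the analysis plan and the registry entry. My preference is the between-arm difference in 24-month change in global mNTB z-score, estimated from the mixed model already planned with the baseline, 12-month and 24-month scores, two-sided at 5%. Keep the proportion of decliners as a supportive analysis, reported as a risk difference or risk ratio so that it speaks directly to the 20% reduction in Section 2.2.

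The cost is wording only; no new data or visits are needed. The downside is that the headline becomes a mean difference and the 20% figure becomes supportive. If the investigators prefer to keep the proportion as primary, they should say so, fix its sidedness, justify the cut at zero, and label the mixed model as secondary.

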#### Cost-effectiveness analysis

2.10.6

A simulation model will be developed to represent the natural history of dementia to assess the cost-utility of the CITA GO-ON Study intervention (Mar et al., 2020). The model will compare two cloned cohorts that had slight differences in progression to dementia according to whether they received the multidomain intervention. It will calculate costs in Euros (€) in each cohort and utility in quality-adjusted life years (QALYs). Finally, the incremental cost-utility ratio (ICUR) will be estimated by dividing the incremental cost (Ca-Cb) by the incremental utility (Ua-Ub). The time horizon will be the lifetime of the patient. A 3% discount rate will be applied to costs and effectiveness. As the main economic impact of dementia is related to the care required as patients become dependent, a societal perspective will be used. Therefore, we will consider direct and indirect costs (Lopez-Bastida et al., 2006), Data for model parameterization will be mainly obtained from the CITA GO-ON study, although some parameters to build the model will be taken from the literature. The NTBm and functional scales (A-IADL-Q) will be used to obtain the model parameters that determine the progression of dementia from the pre-MCI stage to more advanced stages of the disease according to A-IADL-Q cut-off points (MCI < 60, mild dementia < 50 and moderate dementia < 40) (Dubbelman et al., 2022), die from the disease, or die from other causes. Mixed models for repeated measures allow the progression of the scales to be reproduced over time and will be used to simulate the trajectories of real patients (Mar et al., 2020). The model will reflect the improvement introduced by the effectiveness of the intervention in patients to the extent that those treated with multimodal intervention delay their evolution to dementia and improve their health-related quality of life score. We have constructed a preliminary version of the model using a synthetic database. The result has been cross-validated with other nine models within the International Pharmaco-Economic Collaboration on Alzheimer’s Disease (IPECAD) collaboration (Handels et al., 2025).

## Results

3

In July 2021, the CITA GO-ON trial was launched, along with an educational campaign targeting healthy aging practices in the Gipuzkoa region. The campaign was directed towards the capital city of San Sebastian and three smaller municipalities, Deba, Beasain, and Irun. An informational initiative was reached through the direct mail of over 110,000 citizens aged 60 years and above. A robust media presence, including local newspaper advertisements and radio segments, complemented the campaign. Moreover, up to 30 presentations were delivered to neighborhood associations in the specified locales, with a focus on healthy aging and dementia prevention.

The campaign culminated in January 2024, with a preliminary screening of 4,627 individuals via an online survey. Of these, 2,189 people were selected for an in-person screening visit. By this moment, 1736 participants were informed about the study and signed an informed consent form. Of these, 1,051 (60%) were selected for the study (Figure 3). The recruitment phase has concluded in autumn 2024. There were no significant differences (*p* = 0.062) between participants’ self-reported mean CAIDE dementia risk score calculated using the online form [mean, (SD); 7.23 (1.77)] and the in-score calculated at the screening visit [mean, (SD); 76.98 (1.70)]. This finding indicates that the online form may be a reliable tool for assessing the risk of dementia.

**Figure 3 fig3:**
[figure not shown]
CITA GO-ON study recruitment process CONSORT flowchart.

In the ongoing CITA GO-ON trial Intervention period, 465 individuals have been allocated to the Group 1-Regular Health Advice (RHA) group, and 455 have been assigned to the Group 2-Multidomain Intervention (MD-Int) group. Baseline assessments revealed that a substantial majority (approximately 95%) of the participants randomly selected for the trial exhibited modifiable dementia risk factors as identified by their Cardiovascular Risk Factors, Aging, and Dementia (CAIDE) score.

The characteristics of the already screened participants are shown in Table 5. The mean (SD) age of the 68.67 (6.17) of subjects who were screened was 880 (50.7%) women. Selected participants were older and had a higher risk of dementia, as measured by the CAIDE dementia risk score, compared to not selected subjects. Specifically, they had higher systolic blood pressure and body mass index, were less physically active, performed poorly on brief cognitive screening tests, and reported more frequent memory complaints.

**Table 5 tab5:** Age, sex, CAIDE dementia risk score, and brief cognitive tests score of the interested subjects depending on their selection status.

	**Total (*n*: 1736)**	**No selected (*n*: 685)**	**Selected (*n*: 1051)**	*p-value*
Age (years), x(sd)	68.67 (6.17)	67.16 (5.53)	69.65 (6.36)	<0.001
Sex: woman, *n* (%)	880 (50.7)	365 (41.5)	515 (58.5)	0.076
CAIDE dementia risk score	7.16 (1.67)	6.48 (1.786)	7.62 (1.427)	<0.001
Education (years)	13.65 (4.60)	14.87 (4.34)	12.86 (4.60)	<0.001
Systolic blood pressure (mmHg),x (sd)	141.45 (18.55)	137.59 (18.89)	143.99 (18.40)	<0.001
Serum total cholesterol (mmol/l), x (sd)	5.53 (1.09)	5.53 (1.06)	5.53 (1.10)	0.919
Body mass index (kg/m2), x (sd)	23.76 (8.83)	23.03 (8.67)	24.24 (8.92)	0.008
Body mass index > 30 kg/m2, *n* (%)	371 (21.4)	109 (29.4)	262 (70.6)	<0.001
Physicaly inactive, n (%)	633 (36.4)	204 (32.2)	429 (67.8)	<0.001
Fototest, x (sd)	39.55 (5.80)	41.99 (5.03)	38 (5.73)	<0.001
Memory Alteration Test, x (sd)	41.98 (5.34)	44.55 (3.69)	40.35 (5.58)	<0.001
Cognitive Change Index (memory items), x (sd)	21.05 (7.93)	16.95 (5.90)	23.67 (7.96)	<0.001

## Discussion

4

The CITA GO-ON Study is a lifestyle intervention efficacy trial conducted in Southern Europe, which aims to replicate the findings of the FINGER study and ascertain its reproducibility across diverse global populations. It is part of the broader World-Wide FINGERS network (Kivipelto et al., 2018b, 2020), which includes similar initiatives in Latin America (Crivelli et al., 2023), Singapore (Chew et al., 2021), the United States (Baker et al., 2024) and others (Moon et al., 2025; Röhr et al., 2021; Sugimoto et al., 2021; Deckers et al., 2024; Feldman et al., 2023; Gardener et al., 2024; Kumagai et al., 2023). The CITA GO-ON study’s main protocol emanates from a collaborative effort among leading researchers and institutions within our region in each of the intervention domains and the exploratory variables of the study.

In alignment with the FINGER trial methodology (Ngandu et al., 2014), the CITA GO-ON study mirrors its inclusion protocols and outcomes yet diverges in its recruitment strategy. Unlike the FINGER trial, which relied on prior health registries, recruitment in the CITA GO-ON has been community-based. This population-oriented approach is an efficient strategy for identifying adults with modifiable risk factors of dementia and cognitive decline. Our delineation of a “cognitively frail” population was based on the combination of an increased dementia risk profile, as measured by the CAIDE risk score and the presence of early cognitive changes including MCI. These are characterized by relevant subjective memory complaints corroborated by consistent accounts or cognitive performance that falls short of expectations in brief cognitive assessments. Based on this approach, we already observed in the GOIZ ZAINDU pilot study that the greatest effect on cognition is produced in executive and processing speed function, which is consistent with previously reported data from the FINGER trial. We understand that a more prolonged intervention period and a larger sample study will might help us to expand this evidence.

Previous lifestyle intervention studies aimed at dementia prevention underscored the critical nature of participant selection (van Charante et al., 2016; Andrieu et al., 2017), indicating that unselected participants may harbor a similar dementia risk profile to their selected counterparts (Licher et al., 2023). Consequently, by adhering to stringent inclusion criteria, the CITA GO-ON study ensured that the chosen participants exhibited elevated scores on the CAIDE dementia risk index and inferior results on brief cognitive tests (Table 5).

The main protocol of the CITA GO-ON trial, which does not exhaustively delineate them, is comprehensive enough to accommodate ancillary studies. These potential studies will investigate various topics, including alterations in fluid biomarkers, the effects of APOE genotype, blood DNA methylation, sleep quality and quantity and, and a preliminary assessment of the influence of virtual coaches on follow-up.

Blood sample collection and neuroimaging acquisition are conducted in a subgroup of participants who have consented to it (Figure 2). At this point, we have obtained over 700 MRI and blood samples from study participants. This representative subgroup of the study will help us analyze multimodal biomarkers (biofluids and structural neuroimaging). The aim is to evaluate the intervention’s biological impact and identify subjects with a specific clinical-biological phenotype who will benefit most from the intervention. The biofluid samples are not limited to plasma or epigenetic markers. They will include proteomic analyses and explore future options such as metabolomics, genomics, or biomarkers of vascular/synaptic damage. MRI acquisition pre-and post-intervention will assess brain changes, with the possibility of integrating other methods in later phases. This effort is made to create a multimodality unified platform that combines clinical data, biomarkers, and “omics” strategies to analyze the interaction between modifiable risk factors and pathophysiological processes in people at risk of dementia.

### Limitations

4.1

There are some inherent limitations to this type of trials that we have tried to overcome with the study design. Recruitment from a single center for the required sample size represents a significant challenge, demanding innovative strategies to enhance communication and dissemination activities, which are not typically within the realm of clinicians and researchers. This manuscript underscores such innovative strategies, as engaging directly with the target population has led to the development of a more effective study protocol tailored to the specific needs and demands of the population. To ensure the project’s sustainability and the efficient use of resources, the participants were allocated into four waves of 250 individuals for the randomization phase, thereby optimizing resource allocation and preventing resource dilution during periods of low recruitment and overburden during high participants turnout.

Another limitation regarding the recruitment process is the healthy volunteer bias. For that reason, we have included the presence of modifiable dementia risk factors as inclusion criteria; for that reason, we have lost approximately 45% of the interested subjects (Figure 3). Finally, the online prescreening questionnaire may have lost older adults who are digitally illiterate. However, we have made great efforts to avoid it, providing a telephone number in the mass mailing as an alternative. In order to reach communities with poorer communications or poorer accessibility, we also scheduled community talks in rural areas. One of the most challenging issues to achieve in this type of study is blinding. To reduce the impact of this factor, the neuropsychologists responsible for evaluating the primary outcome were not aware of participant assignment to intervention groups, and participants were encouraged not to comment on program details during study visits.

Considering the duration of the project, loss to follow-up was anticipated. The intervention activities were crafted with the participant perspectives in mind, encompassing user-friendly and engaging initiatives, such as the VIVIFRAIL© multicomponent tailored physical activity program. Cognitive training materials called EXERCITA® have also been developed to consider the Basque Country’s cultural and linguistic nuances. Nutritional and culinary workshops led by renowned local chefs and nutritionists aim to provide healthy and appealing culinary skills. In addition to fostering the promotion of socio-emotional skills, the socio-emotional intervention also plays a transversal role in enhancing social commitment, motivation, and adherence to the program. Each follow-up visit dedicated a segment to reiterating the study primary objectives to the participants, addressing any uncertainties or challenges they may have encountered or anticipated.

